### Trial design {8}

The MiGBAN study is a longitudinal, double-blind, randomized, placebo-controlled superiority clinical trial with an observational HC group. Sixty AN patients will systematically be assessed directly after admission (measurement time point TA; pre-interventional baseline measurement), at discharge (TD), after 6 months (T6; post-intervention) and after 12 months (T12). Randomization to either PUFA or placebo will be performed as a stratified block randomization with a 1:1 allocation ratio. Stratification factors are sex, typical/atypical AN and MRI/non-MRI participation. For the 30 HC, only the measurement time points TA and T6 apply, and these participants will not receive any intervention (see Fig. 1 for an overview of the planned trial design). The trial was approved by the local Research Ethics Committee at the University Hospital RWTH Aachen (reference EK 194/19) and will be carried out in accordance with the Declaration of Helsinki. The study was registered at the German Clinical Trials Register (DRKS00017130, 12 November 2019).

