### Outcomes {12}

As co-primary outcomes, BMI (kg/m^2^) and overall microbiota community composition, will be analysed at 12-month follow-up. For microbiota community composition, the primary analysis will be based on beta-diversity within and between PUFA and placebo groups, and individual taxa abundance and alpha-diversity will also be considered. While microbiota characteristics do not have a direct translation into clinical relevance, weight restoration is one of the most important aims in the treatment of AN, justifying BMI as a co-primary outcome. Secondary measures include gastrointestinal symptoms, eating disorder psychopathology and comorbid symptoms (measured via questionnaires), physical activity (number of steps measured via fitness bracelets) as well as serum gut permeability and inflammatory markers. Finally, longitudinal changes of the above measures will be compared between patients with AN and HC using data from all four (two for HC) timepoints.

As previous research found clear alterations in cognitive functioning of patients with AN, especially learning abnormalities and aberrant reward processing (e.g. [33–35]), the trial incorporates neuropsychological tests on executive functioning, flexibility and probabilistic feedback learning all presented on a laptop using Inquisit 5 software (Millisecond Software, Seattle, USA, 2016). These neuropsychological measures are considered exploratory outcomes.

Since the study aims at contributing to a deeper understanding of the gut-brain axis in patients with AN, MRI measurements will be performed at three time points (TA, T6 and T12) in a subgroup of 30 patients and at two time points (TA and T6) for 20 HC. The MRI measurements will consist of structural (grey and white matter) scans and diffusion tensor imaging (DTI) and functional MRI scans. The functional MRI scans will include resting state measurements in order to study functional connectivity plus a probabilistic feedback learning task (based on [36, 37]) similar to the neuropsychological test.

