### Sample size {14}

So far, only one small study investigated the effects of providing PUFA compared to saturated fatty acids in patients with AN and found an effect size in weight gain of *d* = 1.0 [24]. Meta-analyses of probiotic interventions in depression and anxiety disorders revealed a pooled effect size of *d* = 0.68 for improvements in depressive symptoms and *d* = 0.66 for improvements in anxiety symptoms compared to placebo [38]. Thus, for the present study, we assumed an effect size of *d* = 0.8 for the effect of PUFA compared to placebo on BMI. To detect this effect using a two-sided *t*-test with a power of 80% at a significance level of *α* = 0.05, a sample size of 26 patients per group is needed. Considering a rate of loss-to-follow-up until 12 months of 10–15%, 30 patients per group, respectively 60 patients in total will be included in the trial. In case the final analysis will include 30 patients per group, the expected power (assuming an effect size of *d* = 0.8) will be 86%. For effect sizes of *d* = 1.0 and *d* = 0.65 as reported by previous studies mentioned above, the power will be 97% and 70%, respectively. No previous studies providing effect sizes for microbiome composition are available, but the direct effect of PUFA on microbiome composition can be expected to be at least as strong as the indirect effect on BMI.

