## Assignment of interventions: allocation

### Sequence generation {16a}

The allocation sequence that randomly assigns patients to either PUFA or placebo is based on computer-generated random numbers using the R package randomizeR [41]. A stratified block randomization with an allocation ratio of 1:1 is used including the following 5 strata: female typical AN/MRI, female typical AN/no MRI, female atypical AN/MRI, female atypical AN/no MRI, and male patients. The block size is 2 for female patients with a diagnosis of atypical AN and male patients and 4 for female patients with a diagnosis of typical AN.

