## Statistical methods

### Statistical methods for primary and secondary outcomes {20a}

#### Primary and secondary outcomes

For the co-primary outcome microbiome, the overall community composition will be compared between PUFA and placebo groups using non-parametric analysis based on beta-diversity (Permutational Multivariate Analysis of Variance Using Distance Matrices, [60]), including relevant baseline covariates age, sex, atypical/typical AN, and BMI at admission. For the other co-primary outcome measure BMI (at 12-month follow-up) a mixed-effects model repeated measures analysis will be used to test for superiority of the PUFA treatment vs. placebo. This model will include the covariates age, sex, atypical/typical AN, and BMI at admission. Any available further measurements of BMI (in particular at discharge and month six) will be used. As this is equivalent to a phase II trial, emphasis will be on the 95% confidence intervals of the effect size estimates. Moreover, *p* values will be calculated. For further exploratory analyses of microbiome data, see below.

Secondary outcomes such as eating disorder pathology will be analysed in an analogous way to the primary BMI analysis, additionally adjusting for baseline values of the outcome measure (at admission).

Furthermore, individual taxa abundances will be compared between PUFA and placebo groups using mixed models that account for, e.g. age, sex, medication and baseline or time-specific clinical covariates such as BMI and psychopathology. Correlations between diversity parameters and patient data within time points will be assessed via generalized linear models, whereas mixed models will be applied to assess relationships across time points. Exploratory analyses will associate microbiota community composition data at admission with clinical outcomes and identify characteristics of treatment responders vs. non-responders using “indicator-species” analysis and predictive machine learning algorithms (e.g. random forest models).

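### MRI participation is a stratification factor in the randomisation but is missing from the covariates of both co-primary analyses; if it is prognostic, the BMI analysis is mildly conservative

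*Protocol article*

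**What the plan says.** **Randomisation.** The section Trial design {8} states: "Stratification factors are sex, typical/atypical AN and MRI/non-MRI participation". Sequence generation {16a} gives the strata actually used: "female typical AN/MRI, female typical AN/no MRI, female atypical AN/MRI, female atypical AN/no MRI, and male patients". MRI participation therefore splits the four female strata. Male patients form one stratum, divided neither by MRI participation nor by AN type. On blocks the same section says: "The block size is 2 for female patients with a diagnosis of atypical AN and male patients and 4 for female patients with a diagnosis", the last group being the typical-AN females.

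**Analysis.** Primary and secondary outcomes, under Statistical methods {20a}, lists the covariates for both co-primary analyses. For the PERMANOVA on community composition it reads "including relevant baseline covariates age, sex, atypical/typical AN, and BMI at admission". For BMI at 12 months it reads "This model will include the covariates age, sex, atypical/typical AN, and BMI at admission". Secondary outcomes are handled like BMI, with the baseline value of each outcome added. The section also says that the emphasis will be on 95% confidence intervals of the effect estimates.

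**Size of the MRI group.** Outcomes {12} plans MRI "in a subgroup of 30 patients and at two time points (TA and T6) for 20 HC", so half of the 60 patients are to be scanned.

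**The concern.** Blocking within strata keeps the arms close to balanced on MRI status. That balance removes most of the MRI factor's contribution from the true variance of the treatment difference. A model without the factor does not know this: it leaves the MRI variance in the residual and computes its standard error as if the arms could have been imbalanced on MRI status by chance. If MRI status predicts the outcome, the reported standard error then exceeds the real one.

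What is at stake is precision. Intervals become wider than the design warrants, in a plan that puts its weight on intervals, and some of the benefit of the stratification is not collected. A prognostic difference is possible, because scanning needs separate consent and screening for contraindications, so participants are a selected group. The documents do not show that such a difference exists.

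**Working it through.** **1. The plan's own figures.** Sample size {14} states "we assumed an effect size of *d* = 0.8 for the effect of PUFA compared to placebo on BMI", with a two-sided t-test, alpha 0.05 and 80% power. The noncentral t calculation gives n = 25.52, so 26 per group, as stated. With 30 per group, power is 86.1% at d = 0.8, 96.8% at d = 1.0 and 69.7% at d = 0.65, against the stated 86%, 97% and 70%. For dropout, 26/0.90 = 28.9 and 26/0.85 = 30.6, so 30 per group fits the stated range of 10–15%. All these figures reproduce.

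**2. Set-up for the MRI question.**
- From the article: five strata, blocks of 4 for typical-AN females and of 2 otherwise, 1:1 allocation, N = 60, about half in the MRI group, and adjustment for age, sex, AN type and admission BMI.
- Assumed, because the article does not give them: 4 males, 12 patients with atypical AN, complete data, and one linear model at 12 months standing in for the month-12 contrast of the mixed model.
- Also assumed: R², the share of the residual variance (after the listed covariates) that MRI participation explains. With half the patients in each group, R² = 0.25 × δ², where δ is the MRI versus non-MRI difference in residual SDs, so δ = 2√R². R² of 0.05, 0.10 and 0.20 means δ of 0.45, 0.63 and 0.89.
- Runs: 10,000 under no effect and 4,000 at a treatment effect of 0.8 residual SD. The Monte Carlo standard error is √(0.05 × 0.95/10,000) = 0.2 points for type I error, and √(0.85 × 0.15/4,000) = 0.6 points for power near 85%.

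**3. Results, without / with the MRI term.**

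| Assumed R² | Type I error | Power at 0.8 |
|---|---|---|
| 0 | 5.1% / 5.0% | 84.6% / 84.6% |
| 0.05 | 4.7% / 5.1% | 85.8% / 86.9% |
| 0.10 | 4.1% / 5.2% | 86.0% / 88.4% |
| 0.20 | 3.4% / 5.1% | 87.3% / 91.5% |
| 0.30 | 2.2% / 4.6% | 88.2% / 94.9% |

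**4. Why this happens.** Without the term, the mean model standard error stays near 0.262 whatever R² is. The actual spread of the estimate falls as R² rises. The ratio of the two is the factor by which the interval is too wide:
- R² 0.05: 0.2625/0.2591 = 1.013, or 1.3% too wide
- R² 0.10: 0.2624/0.2517 = 1.043, or 4.3% too wide
- R² 0.20: 0.2625/0.2397 = 1.095, or 9.5% too wide

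**5. Cross-check.** With 60 − 6 = 54 residual degrees of freedom, the critical value is 2.005. Multiplying it by these ratios gives 2.031, 2.090 and 2.196, whose two-sided tail areas on 54 df are 4.7%, 4.1% and 3.2%. The simulation gave 4.7%, 4.1% and 3.4%.

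The PERMANOVA was not simulated. These figures apply to the BMI model only.

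**The case against.** The case for leaving this alone has several parts.

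- **It is conditional.** A reader might infer that the standard errors and p values are simply wrong for this randomisation. The documents do not support that. At R² = 0 the two models agree, and nothing in the article shows that MRI participation predicts BMI. The contraindications it gives as examples, implants and claustrophobia, have no evident link to BMI outcome. Admission BMI, already in the model, would absorb part of any severity difference. This stands, and it rules out an unconditional claim.
- **The error is on the safe side.** Nobody should infer false-positive inflation or a biased estimate; type I error falls below 5%. This also stands.
- **Planned power is not undercut.** The trial was sized for 80% power with an unadjusted t-test. With 0.8 scaled to the full residual SD, power without the term stays at 84.6% or above. What is given up is a gain that the stratification made available. This stands for that scaling. If MRI variance were added on top of a unit SD, power without the term would fall as that variance grew.
- **The permutation scheme.** A reader might also infer that PERMANOVA permutations ignore the strata. The article names the method and the covariates but not the scheme, and an article may leave that to the analysis plan. No criticism is made of it.

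The objection does not remove the mismatch itself. The covariate lists for the two co-primary analyses are stated outright rather than deferred or given as examples. They take in two stratification factors and leave out the third without a reason.

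**Conclusion.** The omission is documented, and the point holds in a limited form. MRI participation shapes four of the five strata but is in neither co-primary covariate list nor, by analogy, in the secondary models. If it is prognostic after the listed covariates, the BMI analysis is conservative: at an assumed R² of 0.10, about 1 point of type I error and 2 points of power. Over R² from 0.05 to 0.20, 1 to 4 points of power are forgone. At R² = 0 there is no effect.

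The sizes rest on the assumed R², the assumed numbers of males and atypical patients, complete data and a single-timepoint model. An R² of 0.10 already requires a difference of 0.63 residual SD between scanned and unscanned patients, so the smaller effects are at least as credible as the larger ones. For the PERMANOVA, only the missing covariate is established; its consequence was not quantified. Severity is minor, and the reason to act is that correction costs almost nothing.

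**What to change.** Add MRI participation (yes/no) as a fixed effect to the BMI mixed model, the PERMANOVA and the analogous secondary models. This costs one degree of freedom. In the simulation it brought type I error back to about 5% for R² up to 0.20 and lost no power when MRI participation was not prognostic.

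Alternatively, replace sex and AN type with the five-level randomisation stratum. This follows the allocation most closely. It uses 4 degrees of freedom in place of 2, so about two extra, and it no longer separates typical from atypical AN among males.

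If the omission is intended, one sentence giving the reason would do. Any of these is a change of analysis wording, best made before unblinding, with no effect on trial conduct.

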#### Neuroimaging data

A Hierarchical Gaussian Filter (HGF) will be used to study reward sensitivity and cognitive flexibility during the functional MRI PRL task, in particular in the mesocorticolimbic circuitry, with a Bayesian brain perspective. The functional MRI analyses are planned to be conducted using SPM12 (Statistical Parametric Mapping, Wellcome Trust Centre for Neuroimaging, London, UK) and the HGF analyses will be performed with the help of open-source TAPAS software suite (developed by the Translational Neuromodeling Unit, Zurich, Switzerland) for MATLAB (The MathWorks Inc., MA, USA). The longitudinal study design allows to disentangle state and trait effects of AN that might be found in patients’ feedback learning and reward processing. Neuroplastic effects in resting state functional MRI connectivity will be analysed in the context of dynamic functional connectivity approaches with dynamic Bayesian network and graph analysis methods. Voxel-wise statistical analysis of white matter will be analysed concerning its global and regional fractional anisotropy by means of DTI analyses that will be carried out using TBSS (Tract-Based Spatial Statistics, [61]; part of FSL, [62]). Structural MRI will be analysed using Freesurfer image analysis suite (freely available for download online: http://surfer.nmr.mgh.harvard.edu/).

### Interim analyses {21b}

Not applicable as no interim analyses are planned in this trial.

### Methods for additional analyses (e.g. subgroup analyses) {20b}

Not applicable as no additional analyses are planned in this study.

### Methods in analysis to handle protocol non-adherence and any statistical methods to handle missing data {20c}

The primary analysis will be based on the intention-to-treat principle (ITT), including all randomized patients irrespective of the amount of treatment actually received. To follow ITT principle as closely as possible, all participants will be asked to participate in the end-of-treatment and follow-up assessment (at 6 months and 1 year), in particular regarding BMI measurement and providing a stool sample, even if they drop out of treatment, to minimize the amount of missing data. A per-protocol analysis will be performed as sensitivity analysis. To monitor the regular intake of PUFA intervention, the concentration of PUFA in the blood serum will be determined when drawing a blood sample at 6-month follow-up. In this clinical trial, any missing values of the primary outcome variables have to be considered to be missing not at random (MNAR). Patients with very poor response to the intervention and the standard multi-modal treatment of AN that is the same in both arms might be more likely to drop out of treatment and might be more likely not to provide data on the primary outcomes (loss to follow-up). Thus, imputation strategies or analysis methods that rely on the missing at random (MAR) assumption could be anti-conservative. However, every effort will be made to keep missing data as low as possible. In the primary analysis of the primary endpoint, we will use all available measures of the primary outcome BMI at all time points in a mixed-effects model repeated measures analysis.

Sensitivity analyses will be performed to investigate the potential impact of missing data, in particular, by performing a complete case analysis, a pre-specified conservative single imputation approach and by using multiple imputations.

### Plans to give access to the full protocol, participant-level data and statistical code {31c}

After termination of the study and publication of the results, access to the anonymized datasets will be provided upon reasonable request. Furthermore, the code and automated pipeline used for MRI analyses will be published on a public server.

## Oversight and monitoring

### Composition of the coordinating centre and trial steering committee {5d}

The trial steering committee consists of BHD and JS and will be responsible for the supervision of the study. LK acts as local coordinator of inclusion and data acquisition. A close cooperation with the local CTC-A has been established and specific tasks (e.g., blood sample management, participation in data and project management) are taken over by CTC-A employees. The Department of Child and Adolescent Psychiatry Aachen represented by BHD and JS will also function as coordinating centre for all sites of the ERA-NET NEURON consortium.

### Composition of the data monitoring committee, its role and reporting structure {21a}

The data monitoring committee (DMC) consists of AD and [name] (CTC-A). The DMC is independent from the sponsor and the organizers.

### Adverse event reporting and harms {22}

Patients are asked to actively report and are interviewed weekly for any AEs that they might have perceived. Any AEs or SAEs irrespective of relationship to study intervention will be assessed and documented in standardized forms.

### Frequency and plans for auditing trial conduct {23}

Monthly meetings between psychologists and physicians responsible for conducting the study and a representative of the steering committee take place to supervise the practical implementation of the trial and to discuss potentially occurring problems. This procedure is independent from the sponsor, but not from investigators. In addition, a regular and close exchange of practical experience with the consortium partner in Austria will further contribute to a smooth flow of trial conduct.

### Plans for communicating important protocol amendments to relevant parties (e.g. trial participants, ethical committees) {25}

Any changes in the study protocol becoming necessary during the study will require approval by the local Research Ethics Committee at the University Hospital RWTH Aachen. Changes pertaining to already included participants will be communicated to them and their legal guardians.

### Dissemination plans {31a}

It is planned that results will be published in the form of articles in peer-reviewed scientific journals. There are no publication restrictions resulting from funding. After all results are published the anonymized trial data will be available to the public upon request. Moreover, a trial website will be created giving information about the project and the current status of results to the interested public.

## Discussion

Evidence on microbiome-gut-brain interaction is constantly growing indicating a connection between the gut microbiome and several psychiatric disorders [8, 63]. In AN the gut microbiome composition appears to be clearly altered which could potentially be associated with increased gut permeability and inflammation processes found in patients with AN. However, previous studies often lead to heterogeneous results [13, 18]. Thus, systematically investigating the role of an altered microbiome for the course and treatment of AN could lead to a deeper understanding of this disease. For example, it is unknown whether a longer duration of illness influences the composition of the microbiome and whether the dysbiosis itself becomes a self-perpetuating factor facilitating a transition to chronicity. Research conducted on microbiome-gut-brain interaction and its alteration, especially in the early stages of the illness, could be particularly important for the prognosis of this disorder. The gut microbiome could become a biomarker that might help identifying high-risk patients and taking appropriate steps at an early stage of treatment to provide the best treatment for each individual patient. Moreover, we aim to identify new effective therapeutic tools to improve the treatment and quality of life of patients suffering from this severe psychiatric disorder. AN even seems to be a quite “exemplary” disorder to study gut-brain interaction because there is no other mental disease in which nutrition and its changes play such a crucial role in addition to the microbiome-gut-brain axis. Therefore, during the treatment of AN, the gut microbiome might become an essential target during weight rehabilitation to influence food utilization, appetite, and gastrointestinal symptoms as well as neuropsychological functioning and behaviour. After supplementation with PUFA we expect alterations in the gut microbiome of patients approaching the composition of age-matched individuals without an eating disorder. In addition, we hope to improve gastrointestinal complaints and comorbid symptoms like mood and anxiety, to reduce inflammatory processes and to facilitate weight gain after treatment and at 12-month follow-up. All in all, PUFA supplementation could contribute to a better overall therapy outcome if the current clinical trial is successful, and its administration would be a readily applicable additional component of multimodal AN treatment.

